# **Analysis plan- secondary endpoints**

Analysis of secondary outcome measures will be performed at the end of the trial. Secondary endpoints include;

1. Fever clearance time (Time to first fall  37.50C, axillary, and to remain  37.50C for 48 hours)
2. Time to plasma concentrations of the pro-inflammatory cytokines TNF, IL-6, IL-1B, IL12, IL-8 and the anti-inflammatory, IL-10 to return to normal range (defined a priori)
3. Time to SGOT, SGPT to return to normal range (defined a priori)
4. Time to platelet count to exceed >100,000 per ul

These secondary outcome measures will be analysed by Kaplan-Meier estimates with comparison of curves between treatment groups using log-rank test. Adjusted treatment effect will be estimated and independent predictors will be identified using Cox regression analysis with stepwise forward variable selection procedure.

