**Study Aims**

To measure the antiviral efficacy of chloroquine in the treatment of dengue.

Primary endpoint

The primary endpoint is;

1. time to negative DENV NS1 antigenaemia in plasma
2. time to negative reverse transcriptase (RT)-PCR detection of viral RNA in plasma

For the purposes of the study, time to a negative NS1 or PCR will be the interval between starting treatment and the first time NS1 or PCR is negative and remains negative for two consecutive measurements.

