**Patient selection:**

Patients will be eligible to be admitted to the study if they have suspected uncomplicated dengue and:

1. Are >14 years of age
2. They have a history of symptoms of 3 days or less.
3. They give fully informed consent.
4. No previous history of hypersensitivity to Chloroquine
5. They are not pregnant.
6. They are not G6PD deficient
7. They are not receiving therapy for other disorders

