# **Analysis plan- primary endpoints**

Baseline variables at randomization will be compared between the 2 treatment groups and analysed using the Kruskal-Wallis test for continuous variables and the chi-square test (or Fisher’s exact test) for categorical variables. Only study subjects who have detectable NS1 antigenaemia or viraemia (detected by PCR) at the time of study entry will be analysed for the primary endpoint measures. The primary endpoints are time to negative DENV NS1 antigenaemia in plasma and time to negative reverse transcriptase (RT)-PCR detection of viral RNA in plasma. Comparison of Kaplan-Meier survival curves (representing proportion of cases NS1 or PCR positive) between treatment groups using log-rank test will be performed. Adjusted treatment effect will be estimated and independent predictors will be identified using Cox regression analysis with stepwise forward variable selection procedure.

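### The platelet endpoint can be met at time zero by a patient whose count then falls, and none of the laboratory recovery endpoints requires the recovery to last

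*Protocol*

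**What the plan says.** The section Analysis plan- secondary endpoints lists four kinds of time-to-event outcome.

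- **Platelets (item 4):** "Time to platelet count to exceed >100,000 per ul".
- **Liver enzymes (item 3):** "Time to SGOT, SGPT to return to normal range (defined a priori").
- **Six cytokines (item 2):** time for each, ending with "IL-10 to return to normal range (defined a priori").
- **Fever (item 1):** the only one with a persistence condition. The temperature must come down, "axillary, and to remain" down for 48 hours.

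The analysis is the same for all four: "These secondary outcome measures will be analysed by Kaplan-Meier estimates with comparison of curves between treatment groups using log-rank test", plus Cox regression. No restriction on the patients analysed is given.

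The Patient selection section admits suspected uncomplicated dengue. Its only condition on the course of illness is "They have a history of symptoms of 3 days or less". It sets no platelet or enzyme limit (and none for cytokines).

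For the primary endpoints the protocol is stricter. Study Aims times clearance to "the first time NS1 or PCR is negative and remains negative for two consecutive measurements", and Analysis plan- primary endpoints states: "Only study subjects who have detectable NS1 antigenaemia or viraemia (detected by PCR) at the time of study entry will be analysed" for those endpoints.

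**The concern.** A time-to-recovery endpoint needs three things: a patient who is, or becomes, abnormal; a rule for when recovery has happened; and a rule for those who were never abnormal. The platelet item supplies only a threshold. Patients enter early in their illness, so some may still be above it, and a fall after entry is then invisible to the endpoint. Such a patient is counted as the fastest possible recovery.

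The Kaplan-Meier curve would then mix real recoveries with patients who had not yet worsened. It could not be read as a description of platelet recovery, and any effect of treatment on later falls in patients normal at entry would be missed. For the enzymes and cytokines, one isolated normal value between abnormal ones would end the clock.

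**Working it through.** The protocol gives no figure for these endpoints, so the check is a comparison of definitions.

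| Endpoint | Abnormal at entry required? | Recovery must last? | Patient normal at entry |
|---|---|---|---|
| NS1 and PCR (primary) | Yes: NS1 or viraemia detectable | Yes: two consecutive negatives | Not analysed if neither is detectable |
| Fever | Not stated | Yes: 48 hours | Not stated |
| Cytokines | Not stated | No | Undefined |
| SGOT, SGPT | Not stated | No | Undefined |
| Platelets | Not stated | No | Event at time zero |

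**Platelets.** The event is the first count above 100,000. Take a hypothetical patient with 150,000 at entry and 20,000 on study day 3. The condition holds at entry, so the time is 0 and the day 3 value plays no part. A patient who starts below the cut-off, rises just above it once and falls again is scored as recovered at that one value.

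**Enzymes and cytokines.** A return presupposes an earlier departure, so a patient normal at entry is not automatically at time 0. Three readings are open: time 0, exclusion, or timing to a later return. The a priori definition mentioned in both items covers the normal range and does not settle this. The lack of a persistence rule applies as it does for platelets.

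**Could the data support better definitions?** Yes. Observations and Investigations schedules platelets, SGOT and SGPT daily and cytokines twice daily, so later falls and confirmed recoveries can both be observed.

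**How many patients could be affected?** Let *f* be the share above 100,000 at entry and *g* the share of those who later fall to the cut-off or below. With the planned total of 220:

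- patients scored at time zero = 220 × *f*; the curve then starts at 1 − *f*;
- patients wrongly scored as recovered at time zero = 220 × *f* × *g*.

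Neither share is in the documents. With *f* assumed between 0.3 and 0.7:

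- *f* = 0.3: 220 × 0.3 = 66 at time zero; curve starts at 0.7.
- *f* = 0.5: 220 × 0.5 = 110 at time zero; curve starts at 0.5, so the median time is 0.
- *f* = 0.7: 220 × 0.7 = 154 at time zero; curve starts at 0.3, median again 0.

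The number wrongly scored lies between 0 (*g* = 0) and 66, 110 or 154 respectively (*g* = 1). This shows how the rule behaves; it does not estimate what will happen.

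**The case against.** The strongest reply is that these are secondary laboratory markers in an antiviral trial, and that risk sets and confirmation rules for such markers are commonly left to a statistical analysis plan, which may exist. This has some force for the enzymes and cytokines, where the wording is incomplete rather than wrong. It does not answer the platelet item, which states a full event rule that gives a wrong result when followed. The protocol also fixes persistence for its primary endpoints and for fever in the same list, so a reader would take its absence elsewhere as intended.

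A second reply is that worsening is captured elsewhere. Other secondary endpoints counts severe adverse events judged likely to be due to treatment, dengue shock syndrome, and gastrointestinal bleeds needing transfusion. Those are relevant, but none compares platelet fall or enzyme rise across all patients. It is also true that in a patient abnormal at entry, further worsening delays recovery and so does register. The blind spot is confined to patients normal at entry and to brief crossings.

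Three stronger readings are tempting and are not supported:

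- **That patients with normal enzymes or cytokines also score an instant recovery.** The wording presupposes an earlier abnormality, so their time is undefined.
- **That a definite amount of power is lost.** A figure would need the share normal at entry, which is not given, and a treatment effect on these markers. The hazard ratio of 2 in Sample Size concerns NS1 clearance. No power target is stated for these endpoints, and comparing with an analysis that drops patients normal at entry would not measure the gain from the fix, which keeps them.
- **That the rule favours one arm.** It applies equally to both, and entry status precedes treatment. The fault is in what the endpoint can see and how it can be read.

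**Conclusion.** The point holds in two parts. The platelet endpoint as written scores a patient above 100,000 at entry as recovered at time zero whatever follows, and counts any brief crossing. The SGOT/SGPT and cytokine endpoints lack a persistence condition and leave the time undefined for patients normal at entry.

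The conclusion about wording rests on the text alone. The practical size rests on two unknown shares: those normal at entry, and those among them who later become abnormal. It would be negligible if nearly all patients enter below the cut-off, or if those above it stay there. The primary endpoints and the sample size are untouched. It should be corrected, as a matter of secondary-endpoint definition.

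**What to change.** Define each platelet, SGOT/SGPT and cytokine endpoint as the time from first dose to the first value past the threshold, or in the normal range, that is

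- confirmed by at least the next consecutive measurement, and
- not followed by an abnormal value within follow-up.

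Censor patients who do not meet this at their last measurement. A single normal value at the last visit then does not count. Patients never abnormal are given time 0. Patients normal at entry who later become abnormal are timed to their confirmed recovery.

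The never-abnormal patients still sit at time 0. The fix does not remove them; it stops patients who worsen from being counted with them. Restricting the analysis to patients who become abnormal after entry would not be a sound alternative, because that selects on something treatment may influence.

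In all analysed patients, also compare platelet nadir and peak SGOT/SGPT between arms, adjusted for the entry value. This shows the worsening that a recovery time cannot.

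Cost: a protocol wording change and a little more programming, using the daily and twice-daily values already planned. The stricter rule will leave a few more patients censored at day 5, mainly those whose first normal value comes too late to be confirmed.

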**Other secondary endpoints include;**

1. Frequency of grade 3 and 4 adverse events as defined in Appendix 1 that are probably or definitely related to the intervention will be compared between treatment groups.
2. Frequency of new, clinically significant complications after commencement of treatment, including;
   1. Dengue shock syndrome as defined by WHO criteria
   2. Gastrointestinal bleeding requiring transfusion with blood or blood products
3. ELISPOT assays to measure DENV-specific T cell responses. The magnitude and breadth of DENV-specific T cell responses will be compared between treatment groups.
4. The magnitude of gene expression changes in peripheral blood measured by microarray or RT-PCR will be compared between treatment groups.

Frequencies of these secondary endpoints will be compared between treatment groups**.** Statistical analysis will be by parametric (student t-test) or non-parametric (Mann-Whitney U test) approaches. Comparison of proportions will be performed using chi-square (or Fishers exact) test.

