**Trial monitoring and Adverse events**

There will not be an interim analysis of the trial because of the relatively small sample size. All serious adverse events will be reported to the independent data safety and monitoring committee (DSMC). All adverse events will be recorded in the adverse events form found in the case record forms.

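### The only between-arm comparison of adverse events is limited to grade 3 and 4 events judged probably or definitely drug-related, so other severe events can drop out on attribution alone

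*Protocol*

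**What the plan says.** In the Protocol, under Other secondary endpoints, item 1 compares between arms the "Frequency of grade 3 and 4 adverse events as defined in Appendix 1 that are probably or definitely related to the intervention". An event must therefore pass two tests before the arms are compared: severity (grade 3 or 4) and an individual causality judgement (probable or definite).

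Item 2 of the same list carries no causality condition. It is the "Frequency of new, clinically significant complications after commencement of treatment, including" two named conditions: "Dengue shock syndrome as defined by WHO criteria" and "Gastrointestinal bleeding requiring transfusion with blood or blood products". The section closes by stating that "Frequencies of these secondary endpoints will be compared between treatment groups".

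Under Trial monitoring and Adverse events, "All adverse events will be recorded in the adverse events form found in the case record forms", and "All serious adverse events will be reported to the independent data safety and monitoring committee (DSMC"). Neither sentence plans a comparison by arm.

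Under Analysis plan, secondary endpoints, two laboratory outcomes are compared by log-rank test without attribution: "Time to SGOT, SGPT to return to normal range (defined a priori"), and the time for platelets to rise above 100,000 per ul.

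**The concern.** Randomisation and a blinded placebo arm make case-by-case attribution unnecessary for the main safety comparison: an excess over placebo is the evidence of harm. Item 1 reverses the order, attributing first and comparing afterwards. The blinded assessor does not know which treatment the patient received and must separate a drug effect from acute dengue in a hospitalised patient. Vomiting, bleeding and raised liver enzymes can each plausibly be ascribed to the disease.

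If chloroquine raises the rate of such events and many are ascribed to dengue, the excess shrinks before anyone compares the arms. A null result on item 1 would then say little about safety.

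**Working it through.** **1. Which severe events reach a between-arm comparison?** The protocol states no figure for this endpoint, so the first step is to set the provisions side by side.

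| Severe event attributed to dengue, or judged only possibly related | Compared between arms? |
|---|---|
| Dengue shock syndrome | Yes, item 2 |
| Gastrointestinal bleeding with transfusion | Yes, item 2 |
| Bleeding without transfusion | Not by item 1; by item 2 only if classed as a clinically significant complication, which is not defined further |
| Severe vomiting | Not by item 1; by item 2 on the same condition |
| New grade 3-4 transaminase rise | Not by item 1; the time-to-normal endpoint measures recovery and does not clearly count a patient who is normal at entry and rises later |
| Any serious adverse event | Reported to the DSMC; no comparison by arm stated |

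The gap is therefore severe events outside item 2.

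**2. What could the filter cost?** The inputs are 110 patients per arm (Protocol, Sample Size) and a two-sided 5% level. All event rates and attribution shares below are assumptions, because the protocol gives none. For two proportions with n per arm and p̄ = (p1 + p2)/2:

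power = Φ{ [|p2 − p1| − 1.96·√(2p̄(1 − p̄)/n)] / √[(p1(1 − p1) + p2(1 − p2))/n] }

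Worked case, 10% versus 25%, all events counted:

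- p̄ = 0.175
- null standard error = √(2 × 0.175 × 0.825/110) = 0.0512
- alternative standard error = √((0.09 + 0.1875)/110) = 0.0502
- power = Φ{(0.15 − 1.96 × 0.0512)/0.0502} = Φ(0.99) ≈ 84%

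The filter is then applied in two ways.

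*Uninformative attribution:* the same share f of events is called related in both arms, so the compared rates are f·p1 and f·p2.

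*Informative attribution:* 25% of the background and 80% of the drug-caused excess are called related. For 10% versus 25% this gives 0.25 × 10% = 2.5% on placebo and 2.5% + 0.80 × 15% = 14.5% on chloroquine. For 10% versus 20% it gives 2.5% and 2.5% + 0.80 × 10% = 10.5%.

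| Counting rule | True rates 10% v 25% | Power | True rates 10% v 20% | Power |
|---|---|---|---|---|
| All events | 10% v 25% | 84% | 10% v 20% | 55% |
| Half called related, both arms | 5% v 12.5% | 50% | 5% v 10% | 29% |
| A quarter called related, both arms | 2.5% v 6.25% | 27% | 2.5% v 5% | 16% |
| 25% of background, 80% of excess | 2.5% v 14.5% | 90% | 2.5% v 10.5% | 67% |

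The filter can cut power to about a third of its value (27/84 ≈ 0.32; 16/55 ≈ 0.29) or raise it somewhat. The result turns on the quality of attribution, which the protocol cannot show in advance.

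**The case against.** A reader might infer that harms ascribed to dengue never reach a between-arm comparison. The documents do not support that. Item 2 compares new complications whatever their cause, names a manifestation of dengue itself, and is open-ended. Liver enzyme and platelet recovery are also compared without attribution. This part of the objection stands and confines the point to severe events outside item 2. It does not remove the point: the open-ended wording does not guarantee that any other event is counted, and a recovery time is not an incidence of harm.

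A reader might also infer that fatal events are excluded because the item stops at grade 4. That cannot be established. The grades are set in Appendix 1, which is not in the text available, and its scale may place death in grade 4.

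The power loss is not established either. As the last row of the table shows, a filter that removes mostly background can help, and all-cause counting does add noise. Nor should the filter be read as favouring chloroquine: with blinding, misattribution should be similar in both arms, so the likely damage is lost sensitivity.

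Finally, safety tables are commonly left to a statistical analysis plan, which is not at hand and may contain all-cause counts. Their mere absence from the protocol would be no finding. But the protocol does not leave this open: it writes the causality condition into the endpoint.

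**Conclusion.** The point holds in a limited form. The only adverse-event comparison between arms is conditional on a probable or definite causal judgement, and severe events outside the item 2 complications can leave it for that reason alone. This is a real weakness in one secondary endpoint and should be corrected; it does not touch the efficacy endpoints.

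Its size is uncertain. At 110 per arm and an assumed 10% versus 25%, filtered power could lie between about 27% and about 90%, against 84% with all events counted; for 10% versus 20% the range is about 16% to 67%, against 55%. These figures rest on assumed rates and attribution shares and illustrate the dependence on judgement. They do not estimate the loss in this trial.

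**What to change.** Reword item 1 so that the compared quantity is the proportion of patients with at least one adverse event of grade 3 or higher, regardless of attribution, with an explicit statement that deaths are counted. Use all patients who opened a bottle, which is the protocol's own definition of trial entry under Randomisation and Treatment. Report the difference between arms with a 95% confidence interval. Keep the count of probably or definitely related events as a supporting table, and leave item 2 as it is.

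The cost is wording only, since every adverse event is already recorded in the case record form. The drawback is that background dengue events add noise to the comparison. Randomisation balances them in expectation, and the supporting table retains whatever information attribution carries.

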**Subgroup analysis**

The following sub-group analyses will be performed:

1. Comparison of primary and secondary outcomes for those with primary or secondary dengue
2. Comparison of primary and secondary outcomes for each DENV serotype
3. Comparison of primary outcome for cases with DENV viraemias >10,000 cDNA equivalents per ml at the commencement of treatment
4. Comparison of primary outcome for cases with NS1 antigenaemias >500ng/ml at the commencement of treatment
5. In subjects with at least 4 consecutive positive RT-PCR, we will determine the slope of the line representing changes in viral load over time.

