#### Sample Size

The following assumptions were made in calculating the sample size for EF study:

1. The median time to NS1 and PCR clearance in dengue population with normal standard of care is 72 hours
2. Most (90%) of dengue patients admitted to the trial will be day 3 of illness
3. The average proportion of cases that are NS1 and/or PCR positive on day 3 is 80%
4. At the end of follow-up (5 days after study entry), 20% of cases will still be positive for NS1
5. 10% of patients lost to follow-up

Under these assumptions, the minimum number of NS1 or PCR clearance cases required to be able to detect a 36 hours reduction of median time in Chloroquine arm as compared to standard care arm with a power of 0.8 and type I error 0.05--equivalently a hazard ratio relating to NS1 clearance of 2—is 72. Therefore total number will be 138/{0.8*(1-0.1)*(1-0.1)} =220 or 110 patients in each arm. The effect size in this sample size calculation study is large, but can be justified on the basis that a smaller effect size is unlikely to be clinically significant.

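### Subgroup comparisons made within strata, two of them only above a cut-off, cannot show whether the effect of chloroquine differs between kinds of patient

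*Protocol*

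**What the plan says.** Four items of the protocol's Subgroup analysis section matter here.

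- Item 1: "Comparison of primary and secondary outcomes for those with primary or secondary dengue".
- Item 2: "Comparison of primary and secondary outcomes for each DENV serotype".
- Item 3: "Comparison of primary outcome for cases with DENV viraemias >10,000 cDNA equivalents per ml at the commencement of treatment".
- Item 4: "Comparison of primary outcome for cases with NS1 antigenaemias >500ng/ml at the commencement of treatment".

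The section names no test. The analysis plan sections for the primary and secondary endpoints define comparison as between treatment groups (log-rank and Cox for times; t-test, Mann-Whitney, chi-square or Fisher for the rest). Read together, item 2 is a treatment comparison repeated inside each serotype, and items 3 and 4 are each a treatment comparison in a single high stratum. Item 1 most naturally follows the same pattern.

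The Sample Size section plans for the overall comparison only: "with a power of 0.8 and type I error 0.05", for an effect described as "equivalently a hazard ratio relating to NS1 clearance of 2".

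**The concern.** The usual reason to look at serotype, immune status or baseline viral load is to learn whether the drug works differently in those patients. A significant result in one stratum and a non-significant one in another does not answer that. When the strata share one true effect but each has only part of the events, such a split is common. A reader of the trial report could then believe that chloroquine acts against one serotype and not another when nothing of the kind has been shown.

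Items 3 and 4 have a different fault. Each has only one stratum, so no split can arise, but there is also nothing to set the result against. Whatever they show, they cannot say whether viral load or NS1 at entry changes the effect.

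**Working it through.** **Inputs from the protocol**

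- Sample Size: 220 patients, 1:1; 80% positive on day 3; 90% admitted at day 3; 10% lost; 20% still positive for NS1 at the end of follow-up; type I error 0.05, power 0.8, hazard ratio (HR) 2. The HR matches the medians: "The median time to NS1 and PCR clearance in dengue population with normal standard of care is 72 hours" and a 36-hour reduction, so 72/36 = 2 under exponential times.
- Analysis plan, primary endpoints: only patients positive at entry are analysed, by log-rank test.

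**Assumptions, not in the protocol:** a two-sided test, four serotypes, and the share of events in each stratum.

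**1. The plan's own event number.** Freedman: (1.960 + 0.842)² × [(2 + 1)/(2 − 1)]² = 7.849 × 9 = 70.6, so 71. The protocol gives 72, close enough to confirm the two-sided reading.

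**2. Events expected**

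- With all factors: 220 × 0.8 × 0.9 × 0.9 = 143 evaluable patients; × 0.8 cleared = 114 events.
- Without the day-3 factor: 220 × 0.8 × 0.9 = 158; × 0.8 = 127 events.

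**3. Power in a stratum** with E events (Schoenfeld, 1:1): Φ(√(E/4) × ln 2 − 1.96).

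| Events in stratum | Power at HR 2 |
|---|---|
| 57 (half of 114) | 74.4% |
| 63.5 (half of 127) | 78.9% |
| 28.5 (quarter of 114) | 45.6% |
| 31.75 (quarter of 127) | 49.7% |
| 85.5 (three quarters of 114) | 89.3% |
| 95.25 (three quarters of 127) | 92.3% |

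**4. Chance of a split result when every stratum has HR 2**

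- Two equal strata, 2p(1 − p): 2 × 0.744 × 0.256 = 38% (114 events); 2 × 0.789 × 0.211 = 33% (127).
- 25/75 split, p₁(1 − p₂) + p₂(1 − p₁): 0.456 × 0.107 + 0.893 × 0.544 = 53% (114); 0.497 × 0.077 + 0.923 × 0.503 = 50% (127).
- Four equal serotypes, 1 − p⁴ − (1 − p)⁴: 1 − 0.043 − 0.088 = 87% (114); 1 − 0.061 − 0.064 = 87% (127).

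A log-rank simulation (143 patients, exponential times, control median 72 h, censoring at 120 h, 4,000 runs) gave 39% for equal halves and 87% for four equal serotypes.

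**5. Sensitivity**

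- HR 2, total events from 72 to 138, splits from 50/50 to 10/90 for two strata and from equal to 60/20/15/5 for four: never below 29% for two strata or 77% for four serotypes.
- HR 1.5, same ranges: 35-59% for two strata, 45-65% for four.
- No effect: 2 × 0.05 × 0.95 = 9.5% for two strata; 1 − 0.05⁴ − 0.95⁴ = 18.5% for four.

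**6. What an interaction test could detect.** The standard error of the log ratio of hazard ratios is √(4/E₁ + 4/E₂). The ratio detectable with 80% power is exp(2.80 × SE).

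- 114 events, 50/50: SE = √(4/57 + 4/57) = 0.375; ratio about 2.9.
- 114 events, 20/80: SE = √(4/22.8 + 4/91.2) = 0.468; ratio about 3.7.

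**7. Items 3 and 4** need no arithmetic. Effect modification is a contrast between levels of a factor, and each item supplies one level. The data for the other level will exist: Observations and Investigations provides for quantitative PCR and NS1 levels twice daily.

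**The case against.** The strongest reply is that the protocol states no rule for interpreting subgroups. It nowhere says that a difference in effect will be concluded because one stratum is significant and another is not. The split frequencies above are error rates only under that unstated rule. This stands, and it limits the point: the figures show how little a split result means, not how often the trial will draw a wrong conclusion.

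A reader might go further and infer that differences between subgroups will never be tested, or that the plan will produce false claims by serotype. The protocol does not support either. Interaction tests, exploratory labels and multiplicity rules for subgroups are commonly left to the statistical analysis plan, which is not shown. A reader might also multiply outcomes by strata to count expected false positives. The protocol fixes neither the number of serotypes nor one test per outcome, and Fisher's exact test on rare events can run well below its nominal 5%, so no firm count follows.

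Three further objections hold in part.

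- Item 1 can be read as comparing primary with secondary dengue. That is a reason to reword it; items 2 to 4 carry the point without it.
- The effect in patients with high baseline virus is a legitimate question in itself, and the primary analysis still uses every patient positive at entry. What items 3 and 4 cannot do is show that the effect depends on baseline level.
- Two equal halves would each have 74-79% power, so it would be wrong to call every stratum too small.

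**Conclusion.** The point holds in a limited form. The protocol fixes within-serotype comparisons and two comparisons confined to the high stratum; these are stated methods, not omissions. At a common hazard ratio of 2 and 114 to 127 events, split significance is expected in 33-38% of trials for two equal strata, in 50% or more for a 25/75 split, and in about 87% for four equal serotypes. These figures rest on assumed shares, an assumed four serotypes and a true effect of the planned size. If the drug does nothing they fall to about 10% and 19%. A split must not be read as a difference in effect. For items 3 and 4 the fault is the missing low stratum and does not depend on any of these assumptions.

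The primary comparison is untouched, so the priority is low.

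**What to change.** Reword the Subgroup analysis section as follows.

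- For each of the two primary endpoints, fit a separate Cox model for each factor on all analysed patients, containing treatment, the factor and their interaction. The factors are infection status, serotype, baseline viral load and baseline NS1.
- Enter viral load and NS1 as log10 values. Patients enter the primary analysis with either marker detectable, so some may have an undetectable value of the other. Set such values to a pre-stated number, such as the assay's detection limit. Failing this, report both sides of the two stated cut-offs.
- Report stratum hazard ratios with confidence intervals and the interaction p-value. Base any claim that the effect differs on the interaction alone.
- Show secondary outcomes by subgroup as exploratory estimates.

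The cost is a few sentences and a little analysis work, with no new data. The drawback is low power: at 114 events the interaction test reaches 80% power only for a ratio of hazard ratios of about 2.9 (equal halves) or 3.7 (20/80), so few subgroup claims will be possible.
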